## Abstract

****Background**:**

Since the sixties of the last century, many people from Morocco and Turkey have migrated into the Netherlands. In the last decade, Moroccan and Turkish patients have found their way to organizations for mental health care. However, they often drop out of treatment. Problems in the communication with therapists and different expectations regarding treatment seem to be causal factors for the early drop-out of therapy. In the Netherlands as in other countries courses have been developed for training cultural competence of therapists. Yet, up to now, the effectiveness of increased cultural competence of therapists in reducing drop-out of treatment has not been studied.

****Methods/Design**:**

A randomized clinical trial was started in January 2010. Moroccan and Turkish adult patients who are referred to our outpatient clinics for mood and anxiety disorders are randomly assigned to mental health workers who are trained in a cultural module and to those who are not. The therapists have been trained in the Cultural Formulation and in techniques bridging the (cultural) gap between them and their Moroccan and Turkish patients.

The target number of participants is 150 patients, 75 for each group. Drop-out of treatment is the primary outcome measure. Secondary outcome measures are no-show and patients' perspective of care.

****Discussion**:**

The study will give an answer to the question whether increasing cultural competence of therapists reduces drop-out of treatment in Moroccan and Turkish outpatients with depressive and anxiety disorders.

**Trial Registration:**

The Dutch Cochrane Centre, NTR1989

## Background

Since the beginning of the 1960 s, large groups of male labour immigrants from Morocco and Turkey have come to the Netherlands. In the beginning they left their wives and children behind to be cared for by relatives, later they reunited with their families in the Netherlands. They settled down in the large cities such as Amsterdam, because relatively more unskilled labour jobs were available there. After the reunion with the families there was a decrease in immigration of this kind of immigrants around 1985. However, the migration from Morocco and Turkey unexpectedly rose again because children of the immigrants often married men or women from Morocco or Turkey. This contributed to a prolonged migration. As a result there is a first, a second and a third generation although it is hard to strictly separate these generations [1,2]. In 2010 about 349.000 Moroccans and 384.000 Turkish (first and second generation) reside in The Netherlands [3]. In Amsterdam 9.0% is of Moroccan and 5.2% of the population is of Turkish descent [4]. The Moroccan and Turkish population form the largest group of immigrants in the Netherlands as well as in Amsterdam.

It is known that migration can be a stressful process that can lead to mental illness [5,5]. Previous studies in Belgium and the Netherlands have found that common mental disorders are more prevalent among Moroccan and Turkish immigrants [6,7]. Other studies have shown that these groups have found their way to the mental health services [8,9] but treatment intensity seems to be less favourable [10] and high rates of treatment drop-out were found: 46%, among immigrant patients in specialized mental health service use compared to 24% among Dutch patients [11,12]. The high drop-out rates can lead to higher risks of chronicity of symptoms and prolonged disabilities.

The high drop-out rates among immigrants may be due to language problems, to different interpretations of symptoms and to different expectations of treatment [13]. Adequate treatment can only be given when a firm and steady working-relation can be established. It is thought that training therapists in cultural competences will bridge the gap between immigrant patients and their therapists. Without this competence health practitioners can easily fall prey to errors of diagnosis, inappropriate and poor treatment [14]. Training modules in intercultural competence courses have been developed for (mental) health workers. Therapists learn about the cultural background of specific immigrant groups. They learn to be aware of different notions of health and illness and they are trained in specific intercultural skills. Although widely applied there is, up to now, no evidence that training in cultural competence reduces drop-out of treatment or improves treatment outcome [15,16].

The aim of this study is to test whether a cultural competence training for therapists can reduce the treatment drop-out in Moroccan and Turkish patients with depressive and anxiety disorders in specialized mental health care. In order to test the effectiveness of this course we designed a randomized controlled trial. Our research questions are:

1. Does the intercultural competences training of therapists reduce treatment drop-out rates of Moroccan and Turkish patients with depressive and anxiety disorders in specialized mental health care?

2. Does the intercultural competences training of therapists reduce no-show rates, enhance the patient-therapist working alliance and patients' trust in care?

3. What are determinants of treatment dropout?

## Method/Design

### Study design

This study is a multi-centre randomized controlled trial in which treatment drop-out rates of Moroccan and Turkish immigrants with depressive and anxiety disorders, who are treated by therapists trained in cultural competences, are compared to those who receive regular care. Figure 1 shows the design.

**Figure 1 F1:**
[figure not shown]
**Recruitment and measurement protocol**.

### Recruitment/Setting and locations

Participants are recruited within two outpatient mood disorder clinics in Amsterdam. All new Moroccan and Turkish registries, mostly referred by their general practitioner, are screened on in- and exclusion criteria. If eligible, the new registries are randomized by a research assistant before the intake procedure starts. Then the patients are given an appointment for an intake interview by a therapist from the matching condition. After this intake interview the patients receive study information and the informed consent form from the therapists. Within two weeks after the intake an interviewer contacts a patient by telephone and asks oral consent to participate in the study. If the patient gives permission, an appointment is made for the basic interview in the clinic. If the patient is willing and eligible to participate, a written informed consent is signed.

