### Randomization

The patients are randomized by an independent randomization team that uses a computerized random number generator. The patients are randomly assigned for either intake or treatment to therapists who are trained in cultural competence (the intervention group) or to therapists who are not trained in cultural competence (regular care, control group). The research assistant reveals the treatment condition by telephone to the registration staff who plans the intake interview.

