### Intervention

Therapists of the intervention condition have been trained in cultural competence. The training program is based on existing modules that are widely used in the Netherlands and are based on international and national literature [18-23]. The aim of the module is to train the intervention therapists' knowledge, awareness and skills in diagnosing and treating Moroccan and Turkish patients with depression and anxiety disorders.

To improve the cultural knowledge the therapists are familiarized with the Moroccan and Turkish patients' background and learn about:

• the specific cultural aspect and elements,

• the impact of migration in first and second generation immigrants,

• the migration history,

• the religious background, (health)habits, beliefs, explanations and expectations,

• traditional health care and health workers.

To improve the cultural awareness therapists are taught to:

• be aware of their own cultural background, attitudes and values,

• recognise prejudices and generalizations regarding the cultural background of the patients.

To improve the intercultural skills the therapists are trained:

• how to give psychoeducation

• how to make use of an interpreter during treatment,

• how to make use of the Cultural Formulation [24] during intake and treatment,

• in intercultural diagnostics [25],

• how to use the intercultural addenda to the treatment guidelines for depression and anxiety disorders [26,27].

The module has an interactive character. It contains exercises in becoming aware of the therapists' own cultural background; a discussion about how to deal with traditional health workers; a role play with an actor in using an interpreter and in using the Cultural Formulation during treatment.

The training takes two days. After the training the intervention therapists join a monthly intercultural peer group to keep knowledge, awareness and skills vivid.

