### Analysis

Basic characteristics will be compared between treatment conditions. Dropout will be analysed by (non) parametric longitudinal analysis techniques (eg GLM model) using multivariate statistics. Determinants are modelled along. Analysis will be performed according to the intention-to-treat principle.

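### Randomisation precedes intake, but consent and a second eligibility condition follow it, so a consenters-only analysis would not be intention-to-treat and could lose early drop-outs unequally by arm

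*Protocol article*

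**What the plan says.** The order of events is in the protocol article, Recruitment/Setting and locations:

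1. Screening and allocation: "If eligible, the new registries are randomized by a research assistant before the intake procedure starts".
2. First contact with the allocated condition: "Then the patients are given an appointment for an intake interview by a therapist from the matching condition".
3. Study information: "After this intake interview the patients receive study information and the informed consent form from the therapists".
4. Consent: "Within two weeks after the intake an interviewer contacts a patient by telephone and asks oral consent to participate in the study".
5. Entry, at a basic interview in the clinic: "If the patient is willing and eligible to participate, a written informed consent is signed".

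The Randomization section confirms that the allocation covers intake as well as treatment. The Intervention section lists among the trained skills "how to make use of the Cultural Formulation [24] during intake and treatment", together with intercultural diagnostics. The Analysis section says "Analysis will be performed according to the intention-to-treat principle" and does not define the set. Under Primary outcome measure, drop-out is to be obtained from therapist interviews and medical records.

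**The concern.** Intention-to-treat protects a comparison because membership of the analysed groups is settled before the intervention can act. Here allocation is settled early, but membership of the study appears to be settled after the intake, and the intake is itself part of the intervention. Three things can then differ between arms: who is still reachable up to two weeks later, who agrees after receiving the information from their own arm's therapist, and who is still considered eligible.

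The first is closely related to the primary outcome. A patient who disengages around intake is plausibly also one who does not answer an interviewer's call or come to the clinic for the basic interview. A filter of this kind can remove part of the outcome before counting begins. If it acts differently in the two arms, the effect estimate is biased, and recruiting more patients does not cure that.

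**Working it through.** **Which patients are analysed.** Three places bear on this. Recruitment makes written consent the point of entry. Ethical principles says that participants sign consent. Sample size counts 75 patients per condition to be included. None says that randomised patients who miss intake, are not reached, refuse or are later found ineligible are counted. Together they imply a set of consenters. This is an inference: the set is not defined, and Figure 1 (recruitment and measurement) is not shown in the text available.

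**Inputs.** Drop-out of 45% (control) and 30% (trained), 75 per arm, alpha 0.05 and beta 0.01 come from Sample size. Sidedness is not stated; I use two-sided. The document gives no figure for losses before consent, so every loss below is an assumption. I also assume that all non-drop-outs consent and that there are 75 consenters per arm.

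**The plan's own figure.** For 45% v 30% at beta 0.01, the usual two-proportion formula gives 378 per arm two-sided (324 one-sided), so 75 does not reproduce. That is a separate problem, but it sets the baseline:

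- power = Φ[(d − 1.96·s0)/s1], with s0 = √(2·p̄(1−p̄)/n) and s1 = √([p1(1−p1) + p2(1−p2)]/n)
- d = 0.15, p̄ = 0.375, s0 = 0.0791, s1 = 0.0781
- (0.15 − 0.155)/0.0781 ≈ −0.06, so power ≈ 47%

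**Observed rate among consenters** = (p − a)/(1 − a), where p is the true rate and a is the drop-out, as a share of all randomised, that is lost before consent.

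| Assumed loss before consent | Control | Trained | Difference (control minus trained) | Chance of a significant result |
|---|---|---|---|---|
| None | 45% | 30% | 15 points | 47% |
| 15 v 5 points | 0.30/0.85 = 35.3% | 0.25/0.95 = 26.3% | 9.0 points | 22% |
| 20% of drop-outs in each arm (9 v 6 points) | 0.36/0.91 = 39.6% | 0.24/0.94 = 25.5% | 14.0 points | 45% |
| 10% v 20% of drop-outs (4.5 v 6 points) | 0.405/0.955 = 42.4% | 0.24/0.94 = 25.5% | 16.9 points | 59% |
| No true effect (45% in both arms), 30% v 10% of drop-outs (13.5 v 4.5 points) | 0.315/0.865 = 36.4% | 0.405/0.955 = 42.4% | −6.0 points | 12% (nominal 5%) |

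For the second row: d = 0.0898, s0 = 0.0754, s1 = 0.0750, and (0.0898 − 0.1478)/0.0750 = −0.77, so power ≈ 22%.

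Unequal loss can shrink the difference, enlarge it, or create one where none exists. Equal proportional loss does little.

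**The case against.** The strongest defence is that the article never says only consenters are analysed. It names the intention-to-treat principle, and a condensed article may leave the definition of the set to a fuller document. That stands as a limit on certainty. It does not dispose of the point, because the recruitment order is fixed here, and a later analysis plan cannot restore patients for whom no consent or permission to use records was arranged.

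Four stronger readings are tempting, and the document does not support them.

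- *That the arm's therapist re-judges eligibility.* The article does not say who makes the second judgement. It could be the interviewer: the CIDI diagnosis is listed in Table 1 as a patient interview at baseline.
- *That every early leaver is lost.* Oral consent is asked by an interviewer by telephone and does not require continued attendance, so someone who has left care could still agree, although the basic interview is in the clinic.
- *That those lost are certainly primary events.* The definition requires the therapist to see a need for more therapy and two invitations to go unanswered. Table 1 records drop-out only at the follow-ups, which are timed from the start of treatment. Whether leaving between intake and treatment counts is unclear.
- *That this problem takes power from 99% to 22%.* Power at 75 per arm is already about 47% with no selection. Only the step from 47% to 22% belongs here, and only under the assumed split.

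**Conclusion.** The point holds in conditional form. Entry to the study comes after allocation and after first exposure to the allocated condition. The arm can influence it, and it is plausibly tied to drop-out; that much follows from the stated order of events. If the analysed set is the consenters, the intention-to-treat statement is not met, and early drop-outs may be missing to different degrees in the two arms.

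A reader might infer that the trial will understate the benefit of training. The document does not support a direction: it depends on which arm loses more early leavers, and no loss figures are given. The fall from a 15-point to a 9-point difference illustrates how large the bias could be and is not an estimate. The matter should be settled before analysis because it affects the validity of the primary comparison and can be remedied at modest cost.

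**What to change.** 1. **Preferred.** Define the primary set as all patients randomised, by allocated arm. Fix eligibility at the pre-randomisation screen, with no later exclusion. Take drop-out from the therapist and record sources already in use, subject to ethics committee agreement for patients who did not consent. State how patients who leave before treatment starts, including those who never attend intake, are classed. Because the definition needs the therapist's opinion, a record extract alone may not be enough.
2. **If that is not approved.** Send the study information with the intake appointment, and obtain consent and confirm eligibility before randomising.
3. **Failing both.** Do not call the consenter set intention-to-treat. Report by arm the numbers randomised, seen at intake, found ineligible, not reached and refusing. Add a sensitivity analysis that bounds the effect over a range of assumed drop-out among those not included. Counting every unreached patient as a drop-out is only one end of that range, since some may be in treatment.

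Cost of the preferred option: an ethics amendment and limited extra data collection from records and therapists. Some patients later found to have another main diagnosis stay in the analysis.

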### Randomization

The patients are randomized by an independent randomization team that uses a computerized random number generator. The patients are randomly assigned for either intake or treatment to therapists who are trained in cultural competence (the intervention group) or to therapists who are not trained in cultural competence (regular care, control group). The research assistant reveals the treatment condition by telephone to the registration staff who plans the intake interview.

### Participants

#### Inclusion criteria

Patients (ages 18 to 65) are eligible to participate if:

1. their main problem is a depressive and/or an anxiety disorder for which they are referred to the participating outpatient mood disorder clinics.

2. they are first or second generation Moroccan or Turkish immigrants. The definition for a first generation immigrant is that the patient him- or herself was born in Morocco or Turkey. The definition for the second generation migrant is that at least one of the patient's parents was born in Morocco or Turkey [17].

#### Exclusion criteria

Patients are excluded from the study if their main problem is one of the following disorders: a psychotic disorder, bipolar disorder, organic brain syndrome, substance dependence, or a severe borderline, schizotypical, or antisocial personality disorder.

### Intervention versus control-group therapists

In both clinics six therapists are selected for the intervention group and six for the control group of this study. In both groups disciplines of the therapists, the average amount of years of general treatment experience and ethnic background are evenly distributed.

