### Primary outcome measure

The primary outcome measure is drop-out of treatment. Treatment drop-out is defined as: the patient is in need of more therapy in the therapist's opinion but ignores at least two invitations of the therapist and does not continue the sessions. Data will be gathered by interviewing the therapists and analysing the medical records.

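### No random allocation of therapists to training is described, so randomising patients does not by itself attribute lower drop-out to the training

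*Protocol article*

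**What the plan says.** Four places in the protocol article bear on this.

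- **Aim.** The Background sets out to "test whether a cultural competence training for therapists can reduce the treatment drop-out in Moroccan and Turkish patients". The Discussion paragraph of the Abstract likewise promises an answer on "whether increasing cultural competence of therapists reduces drop-out of treatment". Both are causal statements about training.
- **Patients.** Under Randomization, "The patients are randomized by an independent randomization team that uses a computerized random number generator". They are assigned "to therapists who are trained in cultural competence (the intervention group) or to therapists who are not trained in cultural competence".
- **Therapists.** Under Intervention versus control-group therapists, "In both clinics six therapists are selected for the intervention group and six for the control group of this study". The section adds that across the groups "disciplines of the therapists, the average amount of years of general treatment experience and ethnic background are evenly distributed". It does not say how the selection was made.
- **Limitations.** The section on positive aspects and limitations names therapists' awareness of the intervention and contamination between groups. It does not mention how therapists came to be in one group or the other.

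**The concern.** The training is given to therapists, so each patient's exposure to it is settled by which therapist group the patient is sent to. Patient randomisation makes the two patient groups comparable. It does nothing for the comparability of the therapist groups. Any earlier difference between them in how well they retain patients moves together with training status, and recruiting more patients does not dilute it.

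The primary outcome makes this more than theoretical. A patient counts as a drop-out only if "the patient is in need of more therapy in the therapist's opinion but ignores at least two invitations of the therapist". The therapist's judgement and persistence in inviting are therefore part of the endpoint itself.

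What is at stake is the conclusion. The article's Discussion hopes for a module that other services could adopt if it proves effective. A gain that came from the particular therapists chosen would not travel with the module.

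**Working it through.** **1. What the design identifies.** Write each arm's drop-out as the sum of a patient part, a therapist part and a training part.

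| Part | What makes the arms comparable |
|---|---|
| Patients | Computerised randomisation (Randomization section) |
| Therapists | Stated balance on three characteristics; method of selection not given |
| Training | Fixed by therapist group |

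The difference between arms estimates training effect plus therapist difference. Only the sum is protected by randomisation.

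**2. The planned effect.** The Sample size section assumes 45% against 30%: 45 − 30 = 15 points, and 15/45 = 33%, as stated. The mean is (45 + 30)/2 = 37.5%. The 75 per arm is not reproduced by the error rates given there, but that is a separate matter and this point does not depend on it.

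**3. How large a therapist difference could be.** The article gives no ICC and no information on a shift, so both are assumptions. On the probability scale the therapist SD is sqrt(ICC × p × (1 − p)), with p(1 − p) = 0.375 × 0.625 = 0.2344.

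| Assumed ICC | Therapist SD (points) | Half-SD shift (points) | Share of 15 points |
|---|---|---|---|
| 0.01 | 4.8 | 2.4 | 16% |
| 0.05 | 10.8 | 5.4 | 36% |
| 0.10 | 15.3 | 7.7 | 51% |

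A quarter-SD shift at ICC 0.01 would be only 1.2 points. The shift could go either way.

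**4. What a shift would do to the test.** Suppose training does nothing, and the intervention therapists' usual drop-out is b points below 45%. With 75 patients per arm treated as independent and a pooled two-sided 5% z-test, the chance of a significant result favouring training is Φ((b − 1.96·se0)/se1), where:

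- se0 = sqrt(2·p̄(1 − p̄)/75), with p̄ the mean of the two arm rates;
- se1 = sqrt((p1(1 − p1) + p2(1 − p2))/75), with p1 and p2 the two arm rates.

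For b = 5, se0 = 0.0807 and se1 = 0.0806, so the chance is Φ((0.05 − 0.158)/0.0806) = 9.0%.

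| Assumed b (points) | Chance of false claim for training |
|---|---|
| 0 | 2.5% (nominal) |
| 3 | 5.6% |
| 5 | 9.0% |
| 10 | 23.8% |

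A shift in the opposite direction would hide a real benefit instead.

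**5. What random allocation of therapists would leave.** With k therapists per arm, chance alone gives an SD of the arm difference of sqrt(2/k) × therapist SD. The two clinics give k = 12 if six is a count per clinic, or k = 6 if it is a total.

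| Assumed ICC | k = 12 (points) | k = 6 (points) |
|---|---|---|
| 0.01 | 2.0 | 2.8 |
| 0.05 | 4.4 | 6.25 |
| 0.10 | 6.25 | 8.8 |

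A draw would therefore not make the therapist groups equal. It would make the remaining difference unsystematic, so that a therapist random effect could account for it in the standard error. A systematic difference from selection is not corrected that way.

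**The case against.** The best defence is that the text says less than a critic may hear in it.

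- **Hand-picking.** A reader might infer that therapists were hand-picked, or that volunteers were trained. The article says neither. It leaves the method open, and a condensed article could conceal a draw. This stands: the supportable statement is that no random allocation of therapists is described.
- **Imbalance.** A reader might infer that motivation, interest in migrant patients, earlier intercultural training or usual drop-out differ between the groups, and in favour of training. The article is silent on all four, and silence is not imbalance. This also stands, so no direction can be claimed.
- **Balance was sought.** The three stated characteristics are sensible ones, and balancing them reduces confounding. They do not cover everything that could drive retention, and years of general experience are not experience with these patients.
- **A draw would not help much.** As step 5 shows, chance differences under a draw are of similar size to the illustrated shifts. That is fair for a single trial. The gain from a draw is valid inference, not a guaranteed small error.
- **It is too late.** The article reports a start in January 2010 and describes therapists as already trained. For them, only analysis and wording remain open.
- **The contrast is already worded properly.** The Study design section does compare patients of trained therapists with patients in regular care. The aim and the Abstract go further and speak of the effect of training.

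**Conclusion.** The concern holds in limited form. As described, the design supports a randomised comparison of two sets of therapists. It does not by itself support a randomised effect of training, and the article neither restricts its conclusion accordingly nor lists the limitation.

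A reader might go further and call the whole comparison invalid. The article does not support that: patients are randomised, and the between-group contrast is sound as a contrast between therapist groups.

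The size of any bias cannot be computed from the article. The half-SD illustrations of 2.4 to 7.7 points rest on an assumed shift and on assumed ICCs of 0.01 to 0.10, with direction unknown. The design argument needs none of these figures. It rests on one reading, that selection did not mean a random draw, and would fall away if it did.

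**What to change.** 1. **State how therapists were allocated.** If chance decided, one sentence closes the attribution concern.
2. **Any therapists not yet trained:** pair them within clinic on discipline, experience and ethnic background, and have the randomisation team draw who in each pair is trained. The cost is one draw. The downside is that some less willing therapists may be drawn.
3. **Therapists already trained:**
   - Fit therapist as a random effect. This addresses the standard error, not selection.
   - Add a sensitivity analysis with one or two therapist-level covariates, for example pre-training drop-out or no-show. Past drop-out may be only partly recoverable, because the definition uses the therapist's opinion and data from therapist interviews. With at most 24 therapists and about 56 expected events (75 × 0.45 + 75 × 0.30 = 56.25), the adjustment will be imprecise and cannot remove unmeasured differences.
   - The cost is a record extraction and some modelling.
4. **Limitations and conclusion:** list therapist selection beside awareness and contamination, and word the result as a comparison of trained with untrained therapists, not as a randomised effect of training. This costs only wording and matters most at this stage.
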